## 1. Background

This is the protocol for the assessing the effectiveness of COVID-19 booster doses in England using community testing through Pillar 2 and the test negative case control design. Many of the methods follow those used recently to assess waning of effectiveness for ChAdOx1-S (Vaxzevria, AstraZeneca) and Pfizer-BioNTech (BNT162b2/ Comirnaty®) vaccines (1).

In the UK, COVID-19 booster vaccines were introduced on 14 September 2021. The UK Joint Committee on Vaccination and Immunisation (JCVI) recommended either a BNT162b2 or a half dose (50µg) of mRNA-1273 (Spikevax, Moderna) vaccine to be given as a booster dose no earlier than 6 months after completion of the primary vaccine course (2).

The initial booster programme is currently for all adults over 50 and those 16-49 years with underlying health conditions that put them at higher risk of severe COVID-19, adult carers and adult household contacts (aged 16 or over) of immunosuppressed individuals, and healthcare workers. On the 30 November 2021 the booster vaccine programme was rolled out to all individual's aged 18 years and over.

## 2. Objectives

### 2.1. Aim

To estimate the effectiveness of COVID-19 booster vaccines against covid-19 related symptoms, hospitalisation and death in adults aged 18-49 years and 50 years and older

### 2.2. Primary objectives

- I. Relative VE of each booster vaccine by primary course vaccine type against symptomatic disease compared to 2 doses
- II. Relative VE of each booster vaccine by primary course vaccine type against hospitalisation following symptomatic disease compared to 2 doses
- III. Relative VE of each booster vaccine by primary course vaccine type against death following symptomatic disease compared to 2 doses

### 2.3 Secondary objectives

- IV. Relative VE compared to the first few days after a booster against symptomatic disease, hospitalisation and death
- V. Absolute VE of each booster vaccine by primary course vaccine type against symptomatic disease, hospitalisation and death compared to 0 doses

### 3. Methods

#### 3.1. Study design

Test-negative case-control design

#### 3.2. Data sources

COVID-19 testing data.

- SARS-CoV-2 Testing Polymerase-chain-reaction (PCR) positive and negative tests from the 08 December 2020 to date of extraction for individuals aged  $\geq 18$  years from the UKHSA Unified Sample Database.
- Exclude any negative tests taken within 7 days of a previous negative test, or where symptoms were recorded, with symptoms within 10 days of symptoms for a previous negative test (likely represent the same episode).
- Exclude any negative tests within 21 days before a positive test (false negatives)
- Exclude any positive and negative tests within 90 days of a previous positive test
- Participants contribute a maximum of one randomly chosen negative test result in the booster follow-up period.
- Data are restricted to persons who had reported symptoms and gave an onset date.
- Samples must be within 10 days after symptom onset (account for reduced sensitivity of PCR testing beyond this period).
- Exclude any positive samples sequenced and found not to be the Delta variant

After these criteria, as applied samples taken from 13 September 2021 (week 37, 2021) will be retained for analysis.

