### 3.4. Study period

13 September 2021 (week 37, 2021- vaccine booster roll-out started) to extract date. For hospitalisation and deaths an earlier date for samples included will be used to allow sufficient time for capture of these events.

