### 3.5. Exposure

Vaccination status will be subdivided as follows.

- I. Unvaccinated: no vaccine received
- II. Primary BNT162b2 course followed by a BNT162b2 booster:
  - a. 0-1 days since booster (PF/MD booster combined)
  - b. 2-6 since booster (PF/MD booster combined)
  - c. 7-13 post booster
  - d. 14-34 days post booster
  - e. 35-69 post booster
  - f. 70+days post booster
- III. Primary ChAdOx1-S course followed by a BNT162b2 booster:
  - a. 0-1 days since booster (PF/MD booster combined)
  - b. 2-6 since booster (PF/MD booster combined)
  - c. 7-13 post booster
  - d. 14-34 days post booster
  - e. 35-69 post booster
- IV. Primary BNT162b2 course followed by a half dose Moderna booster:
  - a. 7-13 days since booster

- b. 14 days + since booster
- V. Primary ChAdOx1-S course followed by a half dose Moderna booster:
  - a. 7-13 days since booster
  - b. 14 days + since booster
- VI. Primary BNT162b2 course given at least 175 days before AND not followed by a booster
- VII. Primary ChAdOx1-S course given at least 175 days before AND not followed by a booster

The first few days following the booster could serve as a useful comparator period to estimate the relative VE of the booster to 2 doses as these may reflect a period before the booster has any effectiveness. This may help with possible differences between populations who receive booster doses compared to those who don't. To avoid possible bias due to testing due to any reactogenicity the first 24 hours following the booster may need to be excluded as has been seen with previous doses. The exact days to be used will be assessed visually by plotting the distribution of cases and controls by days since booster. Comparison will only be made within those receiving the same booster.

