### 3.8. Sample size and analysis frequency

Analysis will be done approximately 5 weeks after the booster program has been introduced to allow time for data to accrue to allow good precision of VE estimates. Analysis will be repeated at approximately 3 week intervals and later analyses will allow inclusion of hospitalisations and then deaths. Initial analyses will not include these end points.

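### Symptomatic-disease controls sampled in the last 21 days before extract are incompletely screened for false negatives, which slightly lowers VE, most of all in the early 70+ day booster band

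*Protocol*

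**What the plan says.** Protocol section 3.2 draws "positive and negative tests from the 08 December 2020 to date of extraction". Among the exclusions it lists "Exclude any negative tests within 21 days before a positive test (false negatives"). It then says that "samples taken from 13 September 2021 (week 37, 2021) will be retained for analysis", with no end date other than extraction.

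Section 3.4 ends the study period at the extract date and makes one exception: "For hospitalisation and deaths an earlier date for samples included will be used to allow sufficient time for capture of these events". The length of that cut-back is not stated, and symptomatic disease has none.

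Section 3.5 divides time since booster into bands. The longest, "70+days post booster", appears only for a BNT162b2 primary course followed by a BNT162b2 booster. Section 7 dates the 14-34, 35-69 and 70+ day bands to 06/12/2021 and gives the study of waning as the reason. Section 3.8 repeats the analysis about every 3 weeks.

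**The concern.** Whether a negative test stays in as a control depends on what happens in the following 21 days. For a negative taken *k* days before extract, with *k* below 21, only *k* of those days have been seen. If the later positive falls after the extract, the negative is kept, although the plan's own rule would class it as a false negative. Section 3.4 recognises the need for follow-up time for hospitalisation and death, but not for the control definition of the first primary objective.

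A false-negative control is a case in disguise and carries the cases' booster odds. With true VE above zero those odds are lower than in genuine controls, so the odds ratio moves towards 1 and VE falls. Adjustment for calendar week of onset (section 3.9) does not remove this, because the contaminated controls sit in the same weeks as the cases. Section 4 mentions PCR misclassification only in general and does not say that screening weakens towards extract.

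What is at stake is the comparison across time-since-booster bands. A band concentrated in recent weeks is pulled down more than one spread over the whole period, and a lower estimate at longer follow-up resembles waning.

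**Working it through.** The protocol gives no VE, precision or contamination figure to reproduce. The check has three steps.

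**1. Dates.** Section 1 states that "COVID-19 booster vaccines were introduced on 14 September 2021". The first possible 70+ day onset is 14 September + 70 days = 23 November 2021. A sample taken that day has its full 21 days of look-ahead on 14 December. For any extract up to 13 December, every 70+ day sample is incompletely screened; on 14 December only the first day's samples are complete.

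**2. Share of each band sampled in the last 21 days.** Assumptions: flat testing, sample date equal to onset date, and a constant daily number of boosters, so that bands fill gradually. On the *n*th day of its existence the 70+ band then holds *n* booster-days, and *N* days hold *N*(*N*+1)/2. The 14-34 band starts on 28 September, fills over 21 days (1+…+21 = 231) and then holds 21 per day, so its last 21 days hold 441.

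| Assumed extract | 70+ band | 14-34 band |
|---|---|---|
| 6 Dec 2021 | 100% | 441/1260 = 35% |
| 13 Dec 2021 | 100% | 441/1407 = 31% |
| 27 Dec 2021 | 1 − 105/630 = 83% | 26% |
| 10 Jan 2022 | 1 − 406/1225 = 67% | 441/1995 = 22% |
| 17 Jan 2022 | 1 − 630/1596 = 61% | 21% |

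Treating each band as full from its first day gives lower shares (70+: 60% on 27 December, 38% on 17 January). The order of the bands is unchanged.

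**3. Effect on VE.** Let *t* be the true odds ratio, *o* the booster odds in genuine controls, and *g* the share of controls that a complete look-ahead would have removed.

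- Boosted controls = (1−*g*)·*o*/(1+*o*) + *g*·*t·o*/(1+*t·o*)
- Unboosted controls = (1−*g*)/(1+*o*) + *g*/(1+*t·o*)
- Observed OR = *t·o* ÷ (boosted/unboosted)

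*Level.* None of *t*, *o* and *g* is in the documents. With true VE 85% and *o* = 1, VE reads 84.8% at *g* = 1%, 84.6% at 2%, 83.9% at 5% and 82.6% at 10%. Over *g* of 0.5-5%, *o* of 0.25-4 and true VE of 50-95%, the fall is about 0.03 to 2.4 points.

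*Gap between bands.* Contamination is partial, because part of the look-ahead has been seen. Suppose an extract on 6 December and retest times uniform over 21 days. On average 79% of the look-ahead is unobserved in the 70+ band and 18% in the 14-34 band. If 5% of negatives would eventually be removed, *g* is 0.79 × 5% = 3.95% and 0.18 × 5% = 0.9%. With true VE 90% and *o* = 1:

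- 70+: 0.1 × 0.5162/0.4838 = 0.1067, VE 89.3%
- 14-34: 0.1 × 0.5037/0.4963 = 0.1015, VE 89.9%

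The gap is about 0.5 points. I repeated this day by day with coverage rising linearly to 50% or 90% at extract, an eventual removal share of 1% or 5%, and retest times uniform or exponential (mean 5 days), averaging log odds ratios with the number in the band as weight:

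| Assumed extract | Spurious gap, 70+ versus 14-34 (VE points) |
|---|---|
| 6 Dec 2021 | 0.07 to 1.3 |
| 14 Dec 2021 | 0.05 to 1.0 |
| 10 Jan 2022 | 0.02 to 0.5 |

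The upper ends need 5% contamination, 90% coverage and uniform retest times together. At 1% contamination no gap exceeds 0.3 points.

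**The case against.** **The size cannot be established from the documents.** This stands. The direction follows from the design; the size rests on assumed inputs.

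**Within one onset week there is no spurious waning.** This stands. If true VE is equal across bands, contamination multiplies each band's odds ratio by the same factor. A gap arises only because the bands have different calendar mixes, which is why it is smaller than the fall in level.

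**Later repeats complete the screening.** This stands as mitigation. With repeats about every 3 weeks, each run completes the look-ahead for the previous run's newest samples. But each report still has its own newest three weeks, and an early 70+ day estimate may be reported before the correction arrives.

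**Not every removed negative is a false negative.** This stands. Some may be true negatives before a new infection, and keeping those is not necessarily an error. The control definition still differs between recent and older weeks.

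**A sensitivity run belongs in an analysis plan.** Only in part. The protocol itself fixes the sample end date in section 3.4, including an exception for two of three outcomes, so the gap is in what it states.

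**Stronger readings that the documents do not support.** A reader might take the largest fall in level, about 2.4 points, as the size of the false waning; it is a worst case for controls at high contamination, not a difference between bands. A reader might also point to the first analysis, about five weeks in, where 21 of some 36 sampling days (58%) are incompletely screened. Section 7 places that analysis after version 2.1 and before the current text, and no 70+ day band could then exist.

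**Conclusion.** The point holds as a small, directional weakness. The 21-day exclusion cannot be completed for symptomatic-disease controls sampled in the last 21 days before extract, and nothing in the protocol covers this. VE in those weeks is biased slightly down in all booster bands when true VE is above zero. The effect is most concentrated in the 70+ day band of one vaccine combination: wholly inside the window for extracts up to about 13-14 December 2021, and less so later.

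Under assumed contamination of 1-5%, the spurious difference between the 70+ and 14-34 day bands is probably about 1 VE point or less; only the most adverse combination on the earliest extract reaches 1.3. It rests on assumed retest timing, coverage, true VE and extract date.

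A reader might infer that any observed waning would be an artefact, or that the symptomatic-disease analysis must stop 21 days before extract. Neither follows. The gap is too small to account for substantial waning, and a mandatory cut-back would trade timeliness for little and empty the 70+ band in early runs.

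**What to change.** Keep the estimate to the extract date for rapid reporting. Add to section 3.4 or 3.9, for example: 'For symptomatic disease, the time-since-booster estimates will be repeated with samples taken up to 21 days before the extract date, so that the 21-day exclusion in 3.2 is complete for every control. Any statement on waning will be checked against this restricted analysis, or reported as provisional where the 70+ day band is empty in it.'

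The cost is one extra model run per report on a date-restricted dataset. The restricted run loses the newest three weeks, about one reporting cycle, so its intervals are wider. It gives no 70+ day estimate for extracts before about 14 December 2021, and a very sparse one just after; the provisional label is for that period.

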### 3.6. Outcomes

- Individuals testing positive for SARS-CoV-2 on PCR who reported symptoms within the preceding 10 days
- Individuals testing positive for SARS-CoV-2 on PCR who report symptoms and have a hospital admission from ECDS within 14 days of testing.
- Individuals testing positive for SARS-CoV-2 on PCR who report symptoms and die within 28 days of testing.

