## 7. Changes to the analysis plan between version 2.1 (the final version before the first booster analysis) and 2.2 (current version)

| Change                                                                            | date       | Reason                                                                                                                                                              |
|-----------------------------------------------------------------------------------|------------|---------------------------------------------------------------------------------------------------------------------------------------------------------------------|
| Addition of 18-49 analysis                                                        | 06/12/2021 | This age group was added to general recommendation for boosting                                                                                                     |
| Maximum of 1 test negative in the follow-up period                                | 06/12/2021 | As the booster period is quite short using up to 4 random negatives is not necessary and using 1 helps ensure independence.                                         |
| Addition of post booster intervals of 14-34,35-69 and 70+ days post vaccination   | 06/12/2021 | More time has now passed to allow potential waning to be assessed.                                                                                                  |
| Change from 140+ days to 175+ days as the comparator follow-up period post dose 2 | 06/12/2021 | The vast majority of boosters given at the time of the study were from 175+ days so this represents a better estimate of the waned post dose 2 level of protection. |

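### The Delta exclusion removes only sequenced non-Delta positives, so in an open-ended study period a rising variant can distort the late time-since-booster bands and may appear as waning

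*Protocol*

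**What the plan says.** Protocol section 3.2 (Data sources) gives the only variant criterion in the plan: "Exclude any positive samples sequenced and found not to be the Delta variant". Section 3.6 defines the symptomatic outcome without reference to variant: "Individuals testing positive for SARS-CoV-2 on PCR who reported symptoms within the preceding 10 days". The hospitalisation and death outcomes are built on the same positives.

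Section 3.4 sets the period as "13 September 2021 (week 37, 2021- vaccine booster roll-out started) to extract date", with an earlier sample date for hospitalisation and death. Section 3.8 adds "Analysis will be repeated at approximately 3 week intervals" and names no last analysis.

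Section 3.5 divides time since booster into bands. The last, "70+days post booster", is listed only for a BNT162b2 primary course with a BNT162b2 booster. Section 7 gives the reason for the longer bands: "More time has now passed to allow potential waning to be assessed".

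Section 3.9 adjusts for calendar week of onset as a covariate and states no week-by-vaccination interaction. Its primary comparator is two doses at least 175 days before onset with no booster. Section 4 lists imperfect PCR sensitivity as a source of misclassification but not variant.

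**The concern.** The exclusion makes sense only if Delta disease is what the study means to measure, yet it does not secure that. It acts on positives that were sequenced and leaves the rest alone. While nearly all infections are Delta, this does no harm. The plan fixes no end date and no variant-share limit, so following it as written would carry the same rule into weeks when another variant circulates.

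The waning comparison is the most exposed part. Time since booster is tied to calendar time: the longest band can be filled only by the latest weeks, whereas 14-34 days also draws on earlier ones. If the variant mix changes late, the bands differ in mix as well as in time since booster, and a difference between them no longer measures waning alone. Section 5 sends the reports to JCVI, so a misread decline would reach a policy reader.

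**Working it through.** The protocol gives no sequencing fraction, variant share or variant-specific effectiveness, so there is no figure of its own to reproduce. Dates come from the protocol; all other inputs are assumptions.

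**1. When each band can first be filled.** Section 1 states: "In the UK, COVID-19 booster vaccines were introduced on 14 September 2021". Adding 35 days gives 19 October 2021; adding 70 days gives 23 November 2021. When the longer bands were added on 6 December 2021, every possible 70+ day observation lay in the preceding 13 days. Adults first eligible on 30 November reach 35 days on 4 January 2022 and 70 days on 8 February 2022.

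**2. What the exclusion leaves behind.** Let v be the non-Delta share of positives and q the fraction sequenced. The non-Delta share of retained cases is

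p = v(1-q) / [v(1-q) + (1-v)].

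- v = 10%: p = 10.0% (q = 0), 0.08/0.98 = 8.2% (q = 20%), 0.05/0.95 = 5.3% (q = 50%).
- v = 50%: p = 50.0%, 0.40/0.90 = 44.4%, 0.25/0.75 = 33.3%.

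**3. Why a week main effect does not help.** Within one week, with p taken in the two-dose comparator cases, the booster odds ratio is

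OR = (1-p)(1-rVE_Delta) + p(1-rVE_variant).

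Take rVE_Delta = 85%, rVE_variant = 30% and q = 20%.

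- v = 10%: 0.918 × 0.15 + 0.082 × 0.70 = 0.195, an rVE of 80.5% in that week.
- v = 50%: 0.556 × 0.15 + 0.444 × 0.70 = 0.394, an rVE of 60.6%.

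The week term raises or lowers the odds of a positive test for boosted and unboosted alike. It leaves this ratio unchanged.

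**4. What the bands would show.** Logistic regression was fitted to expected counts over 15 weeks, with time-since-booster bands and week as a main effect. Assumed: true rVE 85% from day 14 with no waning, 70% boosted by the end, q = 20%. The share is the non-Delta share in the final week.

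| Final-week share | Variant rVE | Weekly growth in variant odds | 14-34 d | 35-69 d | 70+ d | Change, 14-34 to 70+ |
|---|---|---|---|---|---|---|
| 10% | 30% | ×4 | 84.5 | 84.3 | 83.3 | -1.2 |
| 50% | 30% | ×4 | 82.3 | 80.9 | 76.2 | -6.1 |
| 50% | 60% | ×4 | 83.7 | 83.1 | 80.7 | -3.0 |
| 80% | 30% | ×4 | 79.4 | 76.6 | 68.5 | -10.9 |
| 80% | 30% | ×2 | 74.8 | 70.1 | 61.6 | -13.2 |
| any | 85% (equal) | any | 85.0 | 85.0 | 85.0 | 0 |
| 50% | 95% (higher) | ×4 | 85.5 | 85.8 | 86.8 | +1.3 |

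The last column is the false waning. The fall of a single band from 85% is not, because the 14-34 day band is contaminated too: in the second row 70+ days is 8.8 points below the truth, but the false drop between bands is 6.1.

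**5. Without contamination.** If every retained positive is Delta, or sampling stops before another variant circulates, p = 0 and the model returns 85.0 in all three bands.

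**The case against.** Several objections are fair, and most limit the point rather than remove it.

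- *The target is not stated.* The aim, objectives and outcomes never name Delta. A reader might infer that unsequenced positives are counted as Delta; the protocol retains them but does not label them. This stands. The Delta target is implied by the exclusion alone, and the plan should say so outright.
- *Direction.* A reader might infer that a new variant is bound to look like waning. It is not. The primary estimate is relative to two doses, so false waning needs the booster's relative effect to be lower against the variant. This stands.
- *Size.* Shares, sequencing fraction and variant effectiveness all come from outside the protocol, and at a 10% final-week share the effect is only about 1 point. This stands.
- *Sequencing delay.* It is tempting to add that the newest weeks of each extract are the least cleaned because sequences arrive after PCR results. The protocol gives no turnaround time, so that is an assumption, and the point does not need it.
- *Existing protection.* The earlier sample cut-off for hospitalisation and death drops the newest samples for two of the three primary objectives. This stands in part: the cut-off is there for event capture, is not tied to variant share, and moves forward with each extract.
- *Scope.* The 70+ day band exists for one vaccine combination only. For a ChAdOx1-S primary course the longest BNT162b2 band is 35-69 days, and the second row of the table gives 82.3 - 80.9 = 1.4 points there.
- *An SAP may handle it.* A missing sensitivity analysis is therefore not the finding. The finding is the exclusion and open period that the protocol itself fixes.

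**Conclusion.** The point holds in a conditional form. The exclusion is one-sided, the period is open, and adjustment for week does not restore a Delta-only odds ratio. If a non-Delta variant gains share and the booster's relative effectiveness against it is lower, the late bands can show false waning. Under the stated assumptions with variant rVE at 30% and odds quadrupling weekly, this is about 1 point at a 10% final-week share and about 6 points at 50%. It is nil when relative effectiveness is equal and reverses when it is higher. The main exposure is the symptomatic-disease analysis in the 70+ day BNT162b2-BNT162b2 band. The documents do not show that such a shift occurred or how large it would be. They show that the rule as written would not prevent it.

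**What to change.** 1. State in sections 2 and 3.6 that the VE target is Delta disease.
2. Before applying the exclusion, tabulate by week of onset the non-Delta share among sequenced positives. End the sample window, for cases and controls alike, at the week before that share passes a pre-set threshold, and keep that closing week in later repeats. A threshold of 5% is an example and needs justification. At v = 5% and q = 20%, p = 0.04/0.99 = 4.0%, and with variant rVE 30% the within-week odds ratio is 0.960 × 0.15 + 0.040 × 0.70 = 0.172. That is an rVE of 82.8%, so the shift in the worst retained week is about 2 points.
3. Add a sensitivity analysis limited to cases with positive evidence of Delta. It should not replace the main analysis: being sequenced may depend on severity or vaccination status and so bring its own selection.
4. Add variant misclassification to section 4.

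The cost is one rule and one tabulation of data that the existing exclusion already requires. The price is shorter follow-up and fewer cases in the latest weeks, felt mainly in the 70+ day band.
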